# Pregabalin versus placebo in targeting pro-nociceptive mechanisms to prevent chronic pain after whiplash injury in at-risk individuals – a feasibility study for a randomised controlled trial

**DOI:** 10.1186/s13063-018-2450-9

**Published:** 2018-01-17

**Keywords:** Whiplash-associated disorders, Pregabalin, Randomised controlled trial, Feasibility study, Motor vehicle crash

## Abstract

**Background:**

Whiplash-associated disorders (WAD) are an enormous and costly burden to Australian society. Up to 50% of people who experience a whiplash injury will never fully recover. Whiplash is resistant to treatment and no early management approach has yet been shown to prevent chronic pain. The early presence of central sensitization is associated with poor recovery. Pregabalin’s effects on central sensitization indicate the potential to prevent or modulate these processes after whiplash injury and to improve health outcomes, but this has not been investigated. This paper describes the protocol for a feasibility study for a randomised controlled trial of pregabalin plus evidence-based advice compared to placebo plus evidence-based advice for individuals with acute whiplash injury who are at risk of poor recovery.

**Methods:**

This double blind, placebo-controlled randomised feasibility study will examine the feasibility and potential effectiveness of pregabalin and evidence-based advice (intervention) compared to placebo and evidence-based advice (control) for individuals with acute whiplash injury at risk of poor recovery. Thirty participants (15 per group) aged 18–65 years with Grade II WAD, within 48 hours of injury and currently experiencing at least moderate pain (NRS: ≥ 5/10) will be recruited from Emergency Departments of public hospitals in Queensland, Australia. Pregabalin will be commenced at 75 mg bd and titrated up to 300 mg bd as tolerated for 4 weeks followed by 1 week of weaning.

**Results:**

The feasibility of trial procedures will be tested, as well as the potential effect of the intervention on the outcomes. The primary outcome of neck pain intensity at 3 months from randomisation will be compared between the treatment groups using standard analysis of variance techniques.

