### Data analyses

Because of participant numbers and the aims of the study, we will report descriptive analyses. Recruitment rate (number of patients approached, number consenting to participate and number eligible to be randomised) will be reported, as will frequencies and proportions of missing data and participant attrition, both during intervention and follow-up periods.

A model for recruitment to the main trial will be described, including the success of various recruitment strategies, for example, is recruitment easier though EDs or through GP practices using the ‘permission to contact’ system? It will also include how the ED and general practice sites worked together, how to maximise research staffing efficiency in terms of rostering, etc. Relevant factors that could create barriers to subsequent study completion will be described, and strategies to overcome these discussed.

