#### Statistical analysis

Trends in the data will be analysed by our biostatistician blinded to group allocation using intention-to-treat. We will analyse the effect of treatment separately for each outcome using mixed-effects models with random intercepts for individuals to account for correlation of repeated measures within participants. Treatment group will be included as a fixed effect. We will obtain estimates of the effect of the intervention and 95% confidence intervals by constructing linear contrasts to compare the adjusted mean change (continuous variables) or difference in proportions (dichotomous variables) in outcome from baseline to each time point between the pregabalin plus evidence-based advice and placebo plus evidence-based advice groups. Missing data will be examined for patterns of missingness.

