#### Secondary outcomes

Because of participant numbers, we will present descriptive analyses of the secondary outcomes.

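### The abstract and the methods give different analyses for 3-month neck pain, and the methods both model the secondary outcomes and call them descriptive only

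*Protocol article*

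**What the plan says.** Four places in the protocol article bear on this.

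- **Abstract, Results.** The primary outcome, neck pain at 3 months, "will be compared between the treatment groups using standard analysis of variance techniques". Analysis of variance is not mentioned again in the article.
- **Study outcome measures.** The primary outcome is the 0–10 NRS score at 3 months, that is, a level and not a change. The proportion lodging a compensation claim is listed as a secondary outcome.
- **Statistical analysis.** "We will analyse the effect of treatment separately for each outcome using mixed-effects models with random intercepts for individuals". The effect measure is a linear contrast to "compare the adjusted mean change (continuous variables) or difference in proportions (dichotomous variables) in outcome from baseline to each time point", with 95% confidence intervals. The abstract does not mention mixed models.
- **Secondary outcomes (under Data analyses).** Because of the numbers, "we will present descriptive analyses of the secondary outcomes".

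The Specific objectives say that the potential effect on pain will be used to determine the sample size of the definitive trial.

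**The concern.** There are two contradictions. The first concerns the primary outcome: one text compares groups on the 3-month score by analysis of variance, and the other contrasts adjusted change from baseline in a repeated-measures model. The second concerns the secondary outcomes: one text models every outcome with intervals at each visit, and the other only describes them.

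If both texts stand until the data are unblinded, the primary estimate is not uniquely defined, and the choice could follow the result. The study disclaims evidence of effectiveness, but its effect estimate feeds the planning of the full trial, so the ambiguity carries forward. If the modelling sentence is followed literally for the secondary outcomes, a study of 30 people yields a long list of intervals. A few would exclude zero by chance and could be read as signals.

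**Working it through.** There is no plan figure to reproduce: the Sample size section states that no calculation was done. The check is therefore a comparison of the texts, followed by an illustration of the consequence.

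**Can the texts be read as consistent?**

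1. A mixed model might loosely be called an analysis of variance technique. That does not turn a 3-month level into a change from baseline.
2. The order of headings suggests that Statistical analysis was meant for the primary outcome and Secondary outcomes for the rest. The wording does not allow this. It covers each outcome separately and gives a rule for dichotomous variables. The only primary outcome is a continuous score, and the only dichotomous patient-level outcome listed, the compensation claim, is secondary.

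**Size of the gap in the primary estimate**

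Inputs from the article: 15 per arm; SD 1.5 for pain in ED-recruited acute patients in the investigators' other trials (Limitations), used here as the baseline SD. Assumptions not in the article: 3-month SD 2.0, baseline-to-3-month correlation ρ of 0.2 to 0.7, complete data.

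- Common factor: √(2/15) = 0.365.
- *Unadjusted 3-month difference against unadjusted change difference.* They differ by the chance baseline imbalance, with SD = SD_baseline × √(2/15) = 1.5 × 0.365 = 0.55 points. The 95% range is ±1.96 × 0.548 = ±1.07. The gap exceeds 0.5 points in 36% of trials and 1 point in 7%.
- Entry requires pain of at least 5/10, which narrows the baseline spread. Truncating at 5 gives SD 1.13, and the gap SD becomes 1.13 × 0.365 = 0.41, with a 95% range of about ±0.8.
- *Unadjusted 3-month difference against baseline-adjusted difference.* The gap is the regression slope times the imbalance. With ρ = 0.3 the slope is 0.3 × 2.0/1.5 = 0.4, and the gap SD is 0.4 × 0.548 = 0.22.

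**Precision and what is carried into the full trial** (baseline SD 1.5, 3-month SD 2.0)

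- SE of the 3-month difference: 2.0 × 0.365 = 0.73.
- SE of the change difference at ρ = 0.3: √(4 + 2.25 − 1.8) × 0.365 = 0.77.
- SE of the baseline-adjusted difference at ρ = 0.3: 2.0 × √(1 − 0.09) × 0.365 = 0.70.
- Full-trial N per arm for an assumed difference of 1.0 point, two-sided 5%, 80% power: 2 × (1.960 + 0.842)² × SD². From 3-month values (SD² = 4) this is 63. From change scores it is 80 at ρ = 0.2 (SD² = 5.05) and 33 at ρ = 0.7 (SD² = 2.05).

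**Secondary intervals if modelled**

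Continuous outcomes: NRS, NDI, PCS, PDS, DASS, SF-12 and S-LANSS, seven in all, each counted as one score. At four follow-up visits (assumed for S-LANSS, whose visits are not listed) this gives 7 × 4 = 28 contrasts, less the primary = 27. The expected number excluding zero by chance is 27 × 0.05 = 1.35. This expectation does not need independence.

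**The case against.** The strongest defence is that little turns on this. The abstract sentence is generic, and the methods section names one model. Under randomisation both methods target the same expected difference, so neither is biased relative to the other. The study disclaims evidence of effectiveness, is not powered for it, and its analyst is blinded. All of this is true and limits the severity. It does not remove the conflict: the realised estimate, its interval and the handling of missing visits still differ, and that estimate has a stated use.

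The defence is also right about several stronger readings that a reader might infer.

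- *That the modelling rule cannot be carried out.* The rule covers continuous and dichotomous variables and says nothing of counts. That no claim status exists at baseline is only an inference from the outcome list, and the schedule figure is not shown. Even with no claims at baseline, the contrast reduces to a computable difference in follow-up proportions.
- *That a model for a dichotomous outcome could not give a difference in proportions.* No link function is named, and an identity link gives that measure directly.
- *That the gap always equals the baseline imbalance.* This holds only for an unadjusted change. The article says adjusted without saying for what.
- *That a chance finding among the secondary outcomes is close to certain.* A probability of at least one needs independence, which repeated related scores in the same 30 people do not have. The section also announces intervals, not tests.
- *That "Because of participant numbers and the aims of the study, we will report descriptive analyses" is a third competing primary analysis.* That sentence opens a section that goes on to recruitment, missing data and attrition; effect estimation has its own heading.

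**Conclusion.** Both contradictions stand in the text, and neither is a detail that a condensed article leaves to a fuller document: the article states two different things. The consequence is a primary estimate that depends on the sentence followed. The gap has SD 0.55 NRS points between the two unadjusted versions if the baseline SD is 1.5 (0.41 if truncation at entry narrows it), and about 0.22 against a baseline-adjusted version under ρ = 0.3 and 3-month SD 2.0. These figures assume complete data; with dropout the methods would also use different patients and visits. For the secondary outcomes, literal modelling would add about 27 intervals, about 1.35 of them excluding zero by chance.

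Severity is moderate. The documents do not support a claim of bias or of an analysis that cannot be run. They do support the need to settle one analysis before the allocation is known.

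**What to change.** Before unblinding, make these wording changes:

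1. Name one primary analysis in both the abstract and the Statistical analysis section: a mixed model for neck pain NRS over the follow-up visits, with visit and group-by-visit terms, adjusted for baseline NRS and for site, reporting the 3-month contrast with its 95% confidence interval. With baseline NRS as a covariate, the difference in 3-month level and the difference in change are the same number, so the outcome definition and the contrast agree. The visit terms are what a contrast at each time point requires; the article names only treatment group as a fixed effect. Site belongs in the model because each site has its own randomisation schedule.
2. Remove the analysis of variance sentence from the abstract.
3. Restrict the modelling text to neck pain NRS, in place of each outcome, and let the Secondary outcomes section govern the secondary clinical outcomes otherwise: summaries by arm and visit.

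The change needs no more patients or data, and the Trial status section already foresees communicating changes to analyses. The one small loss is confidence intervals on the other secondary outcomes, which the Secondary outcomes section already disclaims.

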**Discussion:**

Feasibility and potential effectiveness data will inform an appropriately powered full trial, which if successful, will provide an effective and cost-effective intervention for a costly and treatment resistant condition. It will also have implications for the early management of other traumatic conditions beyond whiplash.

**Trial registration:**

Clinical Trials Primary Registry: Australian and New Zealand Clinical Trials Registry.

Clinical Trial Registration Number: ACTRN12617000059369.

Date of Registration: 11/01/2017.

Primary Trial Sponsor: The University of Queensland, Brisbane QLD 4072 Australia.

**Electronic supplementary material:**

The online version of this article (10.1186/s13063-018-2450-9) contains supplementary material, which is available to authorized users.

## Background

In the majority of Western countries, whiplash is the most frequent injury resulting from a motor vehicle crash (MVC) [1]. MVCs result in 50 million injuries worldwide and nearly four million emergency department (ED) consultations in the US per year [2]. In Australia, non-hospitalised minor injuries such as whiplash comprise about 72% of all survivable MVC injuries [3], with total annual costs of over $950 million [3]. The cumulative incidence of whiplash injuries resulting from MVCs has increased to over 300/100,000 people in North America and Western Europe since 1990 [4].

Up to 50% of people with whiplash injury will never fully recover [5] and up to 30% will remain moderately to severely disabled [5]. Most recovery, if it occurs, takes place in the first 2–3 months, after which time recovery plateaus [6, 7]. This indicates that early treatment will be crucial for better recovery; yet, existing early treatment approaches are inadequate. Although current clinical guidelines recommend exercise and maintaining activity for acute whiplash [8], several systematic reviews conclude that exercise/activity-based interventions provide only small effects [9–11]. Early multidisciplinary management (mainly physiotherapy and psychology) is also no more effective than usual care [12]. Behavioural interventions, such as education and advice, also demonstrate only small effects [10]. The effectiveness of medication in the early treatment of whiplash has been flagged as an urgent research need for several years [13], including at the International Summit on Whiplash Injury in 2011 [14]. Our analysis of data from the multi-year Bettering the Evaluation and Care of Health (BEACH) study of General Practitioner (GP) activity in Australia found that medications are prescribed for most whiplash cases [15], yet a recent review found no studies to support the effectiveness of any medication for whiplash-associated disorders (WAD) [16].

The most consistent predictor of poor recovery is higher initial levels of pain [17]. The early presence of pro-nociceptive mechanisms (widespread hyperalgesia, allodynia and spinal cord hyperexcitability (via nociceptive withdrawal reflexes) that does not accommodate within a few weeks) are also associated with poor recovery [18]. Some studies indicate that patients with these pro-nociceptive features do not respond as favourably to physical rehabilitation as those without these features [19]. Addressing initial pro-nociceptive mechanisms in the early acute post injury stage may improve long-term outcomes for this patient group.

Pregabalin is an obvious medication choice for this purpose. It acts to reduce central sensitization and, if shown to be effective, would alleviate concerns about prescription opioids by reducing the incidence of chronic pain, and therefore the need for long-term opioid use. The use of opioids in this patient group is a concern; indeed, the misuse of prescription opioids in the US and Canada has been described as a public health crisis, with evidence that a similar problem is developing in Australia [20]. Our research has shown that 39% of prescribed medications for WAD in general practice were opioids [15], with US data showing that early provision of opioids in the hospital ED for MVC injury patients is associated with continued use 6 weeks later [21]. Both findings highlight a potential risk for opioid misuse in this patient group.

Pregabalin, an anti-epileptic drug, reduces excitability of dorsal horn neurons after tissue damage, blocking development of pronociceptive mechanisms. It is a structural analogue of the inhibitory neurotransmitter g-aminobutyric acid, binding to the voltage-gated calcium channels, reducing the release of several excitatory neurotransmitters, and blocking the development of hyperalgesia and central sensitization [22]. Pregabalin is effective for chronic neuropathic pain conditions such as postherpetic neuralgia and painful diabetic neuropathy [23] and fibromyalgia, which has similar underlying pain processes to WAD [23]. However, treatment with pregabalin did not significantly reduce leg pain intensity or improve other outcomes in patients with mainly chronic sciatica, compared with placebo [24]. More importantly for our trial, pregabalin has been shown to prevent the development of chronic pain following acute injury, in the form of surgery. Buvanendran et al. [25] showed that administering pregabalin perioperatively and for 2 weeks postoperatively reduced the incidence of chronic neuropathic pain at 3 and 6 months after total knee arthroplasty, with less opioid consumption and better range of motion during the first 30 days of rehabilitation. Similarly, less pain and improved functional outcomes have been shown for pregabalin following spinal surgery [26, 27]. Recent systematic reviews concluded that use of pregabalin yields reductions in chronic postsurgical pain, is more effective in surgical models associated with pro-nociceptive mechanisms [28], and shows promise in preventing the transition from acute to chronic pain [29, 30]. Notably, pregabalin has positive effects on anxiety [31], indicating the potential to ameliorate symptoms of stress and arousal common after whiplash injury [32].

While surgery differs from the pain due to musculoskeletal injury in many ways, the pro-nociceptive mechanisms involved remain the same. Yet, despite this commonality, no studies have investigated effects of pregabalin following injury or trauma. Given the promising results in surgical populations, there is sufficient evidence to support the hypothesis that pregabalin used in acute whiplash injury may prevent or modulate pro-nociceptive mechanisms and improve health outcomes for this treatment-resistant condition. In light of this, we propose to test the feasibility of conducting a clinical trial of pregabalin for individuals with acute whiplash injury at risk of developing chronic pain.

Initially, we will conduct a feasibility study to hone eligibility criteria, test recruitment strategies, and develop a model for recruitment for the subsequent full scale trial, which is endorsed by the Australian and New Zealand Musculoskeletal Clinical Trials Network.

### Specific objectives

To evaluate feasibility by estimating expected rates of:i.Recruitment (number of patients approached, number consenting to participate, and number eligible to be randomised)ii.Missing data and participant attritionTo test recruitment strategies and develop a model for recruitment to a full trialTo identify relevant factors that could create barriers to subsequent study completion, and develop strategies to overcome theseTo assess the potential effectiveness of pregabalin in reducing pain for patients with acute WAD at risk of poor recovery to determine the adequate sample size for a definitive full-scale effectiveness randomised controlled trial (RCT)To obtain feedback from ED clinicians, local General Practitioners (GPs), trial GPs and patients on their experience with the trial and areas for improvement to inform a full-scale trial

The study will not attempt to provide evidence of clinical effectiveness for pregabalin in people with acute WAD. This is in accordance with the recommendations from the National Institute of Healthcare Research (NIHR) guidelines [33] and the Consolidated Standards of Reporting Trials (CONSORT) for the development of pilot and feasibility studies [34].

## Methods/design

### Design overview

This is a double-blind, randomised, controlled feasibility study, with 30 voluntary participants (15 per group) with acute whiplash (symptoms < 48 hours) randomly allocated to receive either pregabalin and evidence-based advice, or placebo and evidence-based advice in a 1:1 ratio, for 4 weeks followed by 6 days of weaning. Outcomes will be measured at baseline, 5 weeks, and 3, 6 and 12 months post-randomisation. Study flow is illustrated in Fig. 1.

**Fig. 1 Fig1:**
[figure not shown]
Flow chart of study design

The protocol is reported according to the Standard Protocol Items: recommendations for randomized controlled trials (Fig. 3 SPIRIT diagram and Additional file 1: SPIRIT checklist).

### Setting

Public hospitals in Queensland, Australia (Gold Coast University Hospital (GCUH) and Ipswich Hospital), and nearby General Practice clinics.

### Participants

#### Inclusion criteria

Individuals with Grade II WAD and within 48 hours of injuryCurrently experiencing at least moderate pain (visual analogue scale: ≥ 5/10)Aged 18–65 yearsProficient in written and spoken English

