### Limitations

Recruiting through EDs means that our cohort of patients will not be entirely representative of the entire population of whiplash patients. However, by recruiting participants through EDs, we will be most likely to enrol participants with greater pain and distress and therefore at higher risk of poor recovery – the very group we aim to target. Data from our current trials [54] would support this, where patients with acute injury recruited from ED reported average higher pain levels (6.2 ± 1.5) compared to those recruited from primary care and advertisement (4.5 ± 1.0). In addition, we aim to reduce central sensitization beginning in the early aftermath of injury, and ED recruitment allows us to recruit patients within hours of MVC.

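### Entry pain is named on a VAS in one place and an NRS in another, and the baseline pain item behind the change-from-baseline contrast has no stated recall period, so a 24-hour item could span the crash

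*Protocol article*

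**What the plan says.** **Entry criterion.** The Inclusion criteria require "at least moderate pain (visual analogue scale" at 5/10 or more. The abstract's Methods paragraph gives "currently experiencing at least moderate pain (NRS: ≥ 5/10". The cut-off and the time frame (current pain) agree; the instrument does not.

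**Pain outcome.** Study outcome measures defines the primary outcome as average neck pain over the preceding 24 hours on a 0–10 NRS at 3 months. The same 24-hour NRS is a secondary outcome at 5 weeks and at 6 and 12 months.

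**Baseline.** Design overview states: "Outcomes will be measured at baseline, 5 weeks, and 3, 6 and 12 months post-randomisation". No section gives the baseline pain item a recall period of its own. The SPIRIT diagram, which may list the baseline measures, is not shown.

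**Timing.** Patients enter up to 48 hours after injury, and Limitations presents it as an advantage that "ED recruitment allows us to recruit patients within hours of MVC".

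**Analysis.** Statistical analysis contrasts the adjusted mean change "in outcome from baseline to each time point between the pregabalin plus evidence-based advice and placebo plus evidence-based advice groups". The abstract's Results paragraph says instead that 3-month pain "will be compared between the treatment groups using standard analysis of variance techniques", with no mention of change.

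**The concern.** These are two separate points.

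First, a VAS and an NRS are different instruments, and a cut-off of 5 need not select the same patients on each. The proportion of screened patients who are eligible is a named feasibility outcome, and screening takes place in EDs at two hospitals and in GP clinics. Staff should not be able to read the criterion two ways.

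Second, if the 24-hour item is asked a few hours after a crash, most of its window precedes the injury. Some patients may average in the pain-free hours and others may answer only for the time since the crash. The baseline then reflects hours since injury as well as pain, and the change contrast subtracts it. Specific objectives says the pain data are to help size the full trial, so a distorted baseline SD, or a distorted correlation between baseline and follow-up, could carry into that calculation.

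**Working it through.** The article states no sample-size or power figure, so there is none to reproduce. The instrument conflict is settled by setting the two passages side by side, as above. The rest is illustration.

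**Inputs.** From the article: acute ED pain with mean 6.2 and SD 1.5 (Limitations: "reported average higher pain levels (6.2 ± 1.5"), 15 per arm, entry within 48 hours. Prior neck pain that required treatment is an exclusion, so pre-crash pain is taken as 0. Assumed, not in the article: constant pain since the crash, literal averaging, normal scores with no truncation at 5, and 3-month pain Y = 0.4 × P + noise of SD 2, where P is acute pain.

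**1. Size of the dilution.** The 24-hour average at t hours after the crash is P × min(t, 24)/24. For P = 6.2:

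| Hours since crash | 3 | 6 | 12 | 18 | 24 or more |
|---|---|---|---|---|---|
| 24-hour average | 0.78 | 1.55 | 3.1 | 4.65 | 6.2 |

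Nothing changes from 24 hours onward.

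**2. Spread of the baseline.** Let f = min(t, 24)/24, independent of P, and let b = P × f. Then E(b) = 6.2 × E(f), and Var(b) = E(f²) × (6.2² + 1.5²) − E(b)², with 6.2² + 1.5² = 40.69.
- Enrolment uniform over 0–48 h: E(f) = 0.75 and E(f²) = 2/3. Mean 4.65; variance 27.13 − 21.62 = 5.50; SD 2.35. Half the patients are affected.
- Enrolment uniform over 0–12 h: E(f) = 0.25 and E(f²) = 1/12. Mean 1.55; variance 3.39 − 2.40 = 0.99; SD 0.99. All patients are affected.

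**3. Precision of the treatment contrast.** Var(Y) = 0.16 × 2.25 + 4 = 4.36 and Cov(Y, b) = 0.4 × 2.25 × E(f). The change variance is Var(Y) + Var(b) − 2 Cov(Y, b). The covariate-adjusted variance is Var(Y)(1 − ρ²), where ρ is the correlation of Y and b, ignoring the degree of freedom spent. Each SE is √(2 × variance/15).

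| Baseline | ρ | Change variance | SE, change | Adjusted variance | SE, covariate |
|---|---|---|---|---|---|
| Undiluted | 0.29 | 4.36 + 2.25 − 1.80 = 4.81 | 0.80 | 4.00 | 0.73 |
| Diluted, 0–48 h | 0.14 | 4.36 + 5.50 − 1.35 = 8.51 | 1.07 | 4.28 | 0.76 |
| Diluted, 0–12 h | 0.11 | 4.36 + 0.99 − 0.45 = 4.90 | 0.81 | 4.31 | 0.76 |

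Comparing 3-month pain with no baseline gives √(2 × 4.36/15) = 0.76. A simulation of the 0–48 h case with a true difference of −1 returned a mean of −1.00 for the change contrast, with SE 1.06 (diluted) and 0.80 (undiluted). The contrast is unbiased in either case.

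**4. Meaning of the change.** Under these assumptions mean 3-month pain without a treatment effect is 0.4 × 6.2 = 2.48. Change from the undiluted baseline is 2.48 − 6.2 = −3.72. From the 0–12 h diluted baseline it is 2.48 − 1.55 = +0.93, an apparent worsening in patients whose pain fell. So when everyone is seen early, precision hardly suffers but the within-arm change loses its meaning.

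**5. A second assumed scenario.** With follow-up SD 2.5, let the baseline SD go from 1.5 to 2.0 and the correlation from 0.3 to 0.1. Change variance goes from 2.25 + 6.25 − 2.25 = 6.25 to 4 + 6.25 − 1.00 = 9.25, a rise of 48%. Used as a covariate, the degraded baseline gives 6.25 × (1 − 0.01) = 6.19.

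**6. Entry instrument.** If scores were normal with mean 6.2 and SD 1.5, and an NRS were that score rounded, Φ((6.2 − 5)/1.5) = 78.8% would reach 5.0 and Φ((6.2 − 4.5)/1.5) = 87.1% would round to 5 or more: a gap of about 8 in 100.

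**The case against.** The 24-hour recall at baseline is an inference. The article attaches that recall only to follow-up visits, the SPIRIT figure is not shown, and exact item wording is commonly left to the full protocol. This stands, and the point has to be put conditionally.

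A reader might infer that the recall problem also makes the entry threshold ill-defined. It does not: both passages ask about current pain, and only the instrument name differs.

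A reader might also infer that the treatment effect is biased, because hours since injury differ between patients enrolled in the ED and those enrolled later at a GP clinic. The article does not support that. Baseline is completed before allocation, and randomisation is blocked with a separate schedule per site, so any dilution falls on both arms alike in expectation.

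Nor is every patient affected. Entry is allowed up to 48 hours, ED recruitment only permits early enrolment, and the share assessed under 24 hours is unknown.

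The figures are soft. The 8 in 100 treats an NRS as a rounded continuous score and borrows a distribution from patients already recruited to other trials, on an unstated instrument. The 48% rests on assumed SDs and correlations. The SEs rest on literal averaging and on a spread that ignores the cut at 5.

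Finally, the study disclaims evidence of effectiveness and has no power target, and the SD of 3-month pain can be taken straight from the data without a change score. That limits the damage to planning. It does not help the change contrast that the article says it will report.

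**Conclusion.** The point holds in a limited form. The VAS/NRS conflict is certain, minor, and needs reconciling.

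The baseline recall gap is conditional on the 24-hour item being asked at baseline, and it concerns only patients assessed under 24 hours after injury. Where it applies, it costs interpretability and precision, not validity of the randomised comparison. Under the stated assumptions the loss of precision runs from negligible (SE 0.80 to 0.81, all enrolled within 12 hours) to material (0.80 to 1.07, enrolment spread evenly over 48 hours). If patients answer only for the time since injury, there is no loss. The 8-in-100 and 48% figures are illustrations and not estimates for this trial.

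The 3-month primary outcome is itself well defined. What is unsettled is the baseline subtracted from it, and any SD of change or baseline correlation passed on to the full trial. The remedy is close to free and covariate adjustment was the more precise in every scenario above, so the change is worth making.

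**What to change.** 1. Name one instrument for the entry criterion in both the Inclusion criteria and the abstract, and record which one has been used at screening so far. Both passages say only pain; if neck pain is meant, that should be raised as a change in its own right.
2. State the baseline pain item and its recall: current pain, or average pain since the injury. Keep the 24-hour recall for follow-up visits.
3. Estimate the 3-month difference with baseline pain as a covariate, not as a value to subtract, and bring the abstract and Statistical analysis into line on this.
4. For patients already enrolled, the screening current-pain score can serve as the covariate where it was recorded. Note that it is truncated at 5 and that its instrument must be confirmed.
5. When sizing the full trial, use the SD of 3-month pain and the correlation with the redefined baseline, not an SD of change built on a 24-hour baseline.

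**Cost.** One corrected criterion, one clarified question and one sentence of analysis text. Baseline and follow-up items will no longer share a recall period, so within-arm change is not a like-for-like difference; this matters little once baseline is only a covariate. If the full protocol already specifies a post-injury baseline item, step 2 reduces to saying so.
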